### Data analysis

Descriptive statistics, including mean, median, standard deviation, and interquartile range, will be used to summarise antibody concentrations stratified by diagnostic group (TB disease, TB infection, healthy TB-exposed controls, and non-TB lower respiratory tract infections) and age groups (< 2 years, 2 to < 5 years, 5 to < 10 years, and ≥ 10 years). Antigen-specific antibody concentrations will be analysed in relation to the total (nonspecific) antibody concentrations. Comparisons between groups will be made using t-tests or Mann-Whitney *U* tests if normality assumptions are not met. Children with TB disease and infection will be compared with the following groups: all other remaining children combined, healthy TB-exposed children, and children with non-TB lower respiratory tract infections.

To assess the performance of each individual antigen specific antibody feature as a diagnostic assay, sensitivity and specificity will be calculated based on cut-off values determined by the highest Youden’s index. Receiver operating characteristic (ROC) analysis will be performed, and area under the curve (AUC) will be calculated (confidence interval will be determined using the DeLong method).

In subsequent analyses, we aim to evaluate the combined interpretation of antigen-specific antibodies concentrations and properties using different strategies:

Strategy one involves defining cut-off values based on a specificity of ≥ 98%, in accordance with the minimal WHO’s target product profile(TPP) requirement for a biomarker-based detection test. We will calculate the corresponding sensitivity. Similarly, we will determine cut-off values based on a sensitivity of ≥ 66% and calculate the corresponding specificity. To assess the combined interpretation of multiple antigen targets, the test for a specific antibody or antibody property will be scored positive if at least one antibody level against a specific antigen exceeds the cut-off value in an individual’s plasma sample, and negative if all antibody levels against all antigens in a plasma sample are below the cut-off values.

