Another strategy for the combined interpretation of multiple antibody concentrations and properties will involve feature selection using the least absolute shrinkage and selection operator (LASSO). This approach will help identifying the most informative features that could be used in diagnostic assays. To validate the predictive power of the selected features (k features), we will train and evaluate an additional model using only those k features. In a further step, we will include the selection of antibody concentrations and properties in the training of the model. By performing feature selection using LASSO, we aim to maximize prediction performance using all features and select the k most informative features after the training stage. This procedure is based on the concept that selecting the most informative features from a well-performing prediction model will also yield a well-performing prediction model when one only has access to the selected subset of features. Recent advances in machine learning research will enable us to incorporate feature subset selection directly into the training step of a model [54, 55]. Therefore, we optimise not only the prediction performance but also the subset selection of k features during training. The choice of subset size, k, should be based on external constraints. The diverse sensitivities and specificities observed in paediatric TB serological tests make a precise sample size determination challenging. To estimate the sample size for our experiments, we used data generated from a cohort of adults with latent infection (*n* = 20) and active pulmonary disease (*n* = 22) from South Africa [56]. For the analysis of 75 antibody features, linear regression was conducted to assess the association between diagnosis and antibody feature, while controlling for age and gender. For the thirteen features exceeding a false discovery rate threshold of 10%, the partial correlation coefficient of 0.50 or higher was observed between diagnosis and antibody feature. Using this estimate as the effect size of biologically active antibody features, 68 individuals in an independent cohort (34 LTB, 34 ATB) would provide a statistical power of 80% to observe significant differences in top antibody features between tuberculosis infection and disease at an alpha level of 0.0005. This alpha level represents the threshold for significance required by the Bonferroni-Holm correction method, set at 0.0005 to accommodate the testing of 100 antibody features.

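### Youden, 98%-specificity and 66%-sensitivity cut-offs are taken from the data with no separate scoring data or optimism correction stated, so the reported accuracy will look better than it is

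*Protocol article*

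**What the plan says.** Three cut-off rules stand in the Data analysis section of the protocol article.

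- **Single features:** "sensitivity and specificity will be calculated based on cut-off values determined by the highest" Youden's index.
- **Strategy one, fixed specificity:** "Strategy one involves defining cut-off values based on a specificity of ≥ 98%, in accordance with the minimal WHO’s target product profile". The next step is: "We will calculate the corresponding sensitivity".
- **Strategy one, fixed sensitivity:** "we will determine cut-off values based on a sensitivity of ≥ 66% and calculate the corresponding specificity".

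These cut-offs then feed a combination rule, under which a sample is "scored positive if at least one antibody level against a specific antigen exceeds the cut-off value".

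The section's only wording on validation concerns the LASSO strategy: "To validate the predictive power of the selected features (k features), we will train and evaluate an additional model using only those k features". It names no separate data, and it does not cover the cut-off rules.

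The only group sizes in the article are in the sample-size paragraph: "68 individuals in an independent cohort (34 LTB, 34 ATB) would provide a statistical power of 80" per cent. The independence mentioned there is from the adult pilot cohort used for sizing. It does not describe a test set for the cut-offs.

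**The concern.** A cut-off that maximises Youden's index follows the chance features of the sample in which it is found. Scored in that sample, sensitivity plus specificity is too high on average. A cut-off placed where the sample reaches 98% specificity has a related fault: the sample figure is met because the cut-off was put there, so it says nothing about whether the marker would reach 98% in other children.

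Diagnostic performance is the stated aim of the study, and the 98% figure is tied to a WHO requirement. If accuracy is reported as planned, markers will look better than they are. The gap will be widest where groups are smallest, which includes the four age strata.

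The article does not say in so many words that the same children are used twice. It follows from the rules: each takes a point from the data and reads the other measure at that point, and no other sample is mentioned.

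**Working it through.** **1. The plan's own figure.** Inputs from the sample-size paragraph: partial correlation 0.50, two covariates (age, gender), alpha 0.05/100 = 0.0005, power 80%. Two-sided testing is assumed. By Fisher's z:

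n = ((3.481 + 0.842) / atanh(0.50))² + 3 + 2 = (4.322 / 0.5493)² + 5 = 66.9

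That is 67, or 68 in equal groups, and power at 68 is 0.81. The stated size reproduces and is not in dispute. It concerns a group difference between infection and disease, not the precision of sensitivity or specificity.

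**2. Effect size for the check.** Treating r = 0.50 as a simple correlation with equal groups, d = 2r/√(1 − r²) = 1/0.866 = 1.155. With normal data and equal variances, the best attainable J is 2Φ(d/2) − 1 = 0.436.

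**3. Youden cut-off.** In 2,000 simulated studies per row (d = 1.155, direction of the marker fixed), the cut-off was chosen at the highest J. It was then scored in the same sample and against the true distributions.

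| Children per group (assumed) | Apparent J | J in new children | Overstatement |
|---|---|---|---|
| 20 | 0.540 | 0.403 | 0.137 |
| 34 | 0.512 | 0.412 | 0.100 |
| 68 | 0.488 | 0.419 | 0.069 |
| 150 | 0.468 | 0.426 | 0.042 |

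For a weaker marker (d = 0.5) the overstatement is larger: 0.161, 0.124, 0.087 and 0.053. How the excess divides between sensitivity and specificity depends on how tied cut-offs are resolved. With ties broken at random at 34 per group, the apparent pair is about 75.5%/75.8% and the true pair about 70.6%/70.7%.

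**4. Cut-off at ≥98% specificity.** With n controls, the cut-off is the k-th smallest control value, where k = 0.98n rounded up. For a continuous marker, expected specificity in new children is k/(n + 1). Sensitivities are simulated at d = 1.155 with as many cases as controls (4,000 studies per row).

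| Controls (assumed) | k | In-sample specificity | Expected in new children | Chance true specificity <98% | Sensitivity: sample / new children |
|---|---|---|---|---|---|
| 34 | 34 | 100% | 34/35 = 97.1% | 51% | 0.202 / 0.201 |
| 50 | 49 | 98% | 49/51 = 96.1% | 73% | 0.255 / 0.253 |
| 100 | 98 | 98% | 98/101 = 97.0% | 68% | 0.222 / 0.222 |
| 200 | 196 | 98% | 196/201 = 97.5% | 64% | 0.205 / 0.206 |

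The last column shows no bias in sensitivity at the realised cut-off, because the controls alone set it. At a true specificity of 98%, however, sensitivity would be Φ(1.155 − 2.054) = 0.184. The reported 0.20 to 0.25 is therefore too high if presented as sensitivity at 98% specificity.

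**5. Cut-off at ≥66% sensitivity.** This is the mirror case. With k = 0.66n rounded up, 34 cases give 23/34 = 67.6% in the sample against an expected 23/35 = 65.7%. With 100 cases the figures are 66% against 66/101 = 65.3%. Here the sensitivity is met by construction, and the specificity paired with it is overstated as specificity at 66% sensitivity.

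**6. Precision.** If all of 34 controls are negative, the exact lower 95% limit for specificity is 0.025^(1/34) = 89.7%. A lower limit of 98% would need ln(0.025)/ln(0.98) = 182.6, so 183 controls without a single false positive.

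**The case against.** **The detail may sit elsewhere.** This is a condensed article, and a fuller protocol or analysis plan could add resampling. That is possible. But the article does state how accuracy is to be estimated, and the rule as stated is optimistic. Where it turns to validation, it does so only for LASSO. Leaving the interval method to an analysis plan would be no fault in itself.

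**Group sizes are unknown.** This stands. The 34 is the number of children with TB infection in a power calculation. It is not a control count for the accuracy analyses, which also use healthy exposed children, children with non-TB respiratory infection, and all remaining children combined. CITRUS is still recruiting. Larger groups shrink the Youden bias but do not remove it, and age strata work the other way.

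**The 98% rule does not inflate both measures.** This also stands. The optimism there is in specificity, by about 0.5 to 3 points. The overstatement of 0.10 in J belongs to the Youden rule.

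**Stronger readings that the documents do not support.**

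- A reader might infer that a worthless marker could appear to reach 66%/98% by chance. That pair needs J = 0.66 + 0.98 − 1 = 0.64. The best of 100 independent null features at 34 per group averages only about 0.37. Even the best of 528 (33 antigens × 16 detection reagents), treated as independent and with direction chosen from the data, reaches about 0.45.
- A reader might infer that the study plans to declare the WHO target met. The article uses the target to place a cut-off and says that the findings will help to design assays.
- A reader might infer from r = 0.50 that the study cannot find an adequate test. That is a separate sample-size question. The article gives 0.50 as a lower bound for single features and expects to combine features because single antigens lack sensitivity.

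**Conclusion.** The point holds in a limited form. As written, the Youden rule yields sensitivity and specificity that are too high together, by about 0.10 in J at 34 per group, 0.07 at 68 and 0.04 at 150, for normal data with d = 1.155. The bias is larger for weaker markers and smaller strata. At the 98% cut-off, the in-sample specificity cannot serve as evidence on the WHO figure. Expected specificity in new children is 96.1% to 97.5% over 34 to 200 controls, and the paired sensitivity is optimistic only when labelled as sensitivity at 98% specificity.

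These sizes rest on assumed group sizes, normal features with equal variances, and the plain reading that no other data are used to score the cut-offs. The sample-size calculation is unaffected. The analysis should be changed, but the study's design and samples do not need to be.

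**What to change.** Estimate sensitivity and specificity for every data-derived cut-off (Youden, ≥98% specificity, ≥66% sensitivity, and the any-positive combination built on them) by repeated cross-validation or bootstrap optimism correction. Repeat the choice of cut-off inside each resample, and for the combination repeat the whole rule. Report 95% confidence intervals, and compare results with 98% and 66% only on the corrected estimates. Uncorrected figures may be shown beside them if labelled as apparent.

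Deriving cut-offs in CITRUS and scoring them in pTBred, and the reverse, is a useful addition where both cohorts hold the groups compared. It cannot replace resampling for the comparison with non-TB respiratory infection, because those controls come only from ProPAED.

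The cost is extra analysis work, a few sentences in the plan, and somewhat less favourable reported accuracy. No new samples or assays are needed.

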## Discussion

The development of reliable point-of-care tests for detecting TB infection and disease in children is crucial. Serological assays offer a promising approach, as they may be used in a point-of-care test format, making them suitable for widespread implementation in diverse settings [7]. However, there are several hurdles that need to be addressed to advance the development of TB serological assays. One challenge is the incomplete understanding of the immunogenic properties of the numerous potential antigens of *M. tuberculosis*, including proteins and glycolipids [57]. Our study has four main strengths. First, our study will evaluate antibodies against a broad range of protein antigens [41, 45, 46, 58], as well as glycolipids that are believed to play a crucial role in the pathogenesis of *M. tuberculosis* [59, 60].

Second, to overcome the challenge of potential cross-reactivity of antibodies detected in a serological assay for TB with BCG- and non-tuberculous mycobacteria-antigens [25], we will include a large range of antibodies and reduced the overlap between *M. tuberculosis* and BCG/non-tuberculous mycobacteria-antigens selected. Third, there exists substantial interindividual heterogeneity in the antibody response to *M. tuberculosis* [61, 62]. Different individuals may react to different antigens, resulting in relatively low sensitivity but good specificity for each individual antigen serological assays [30, 31, 49]. To account for this heterogeneity, our analysis includes multiple antigen targets, such as cell wall fractions and total lipids, and aims at a combined interpretation of these parameters.

Finally, we will evaluate specific antibody properties, such as antibody isotypes, glycosylation patterns, and FcR binding profiles [12]. So far, IgG is the most extensively studied isotype and has shown the most promising results for use in diagnostic assays to detect TB disease in children. Other isotypes, such as IgA, have gained attention more recently, as these have a protective role in human and animal studies in preventing TB infection [63, 64]. Glycosylation of the Fc region affects the binding affinity of the antibody to the FcRs. Notably, distinct glycosylation patterns have been associated with various stages of TB disease and infection [11]. Lastly, our data analysis is stratified across distinct age groups to accommodate the dynamic nature of TB disease during various developmental stages of children.

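### The DeLong interval for each feature's AUC, in its usual untransformed form, sets the lower limit too high for the better features at 34 per group (minor)

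*Protocol article*

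**What the plan says.** The Data analysis section of the protocol article takes features one at a time ("To assess the performance of each individual antigen specific antibody feature as a diagnostic assay"). For each it plans Youden-based sensitivity and specificity, a ROC curve and an AUC. For the AUC, the "confidence interval will be determined using the DeLong method". The text gives no scale, no confidence level and no rule for a sample AUC of 1.

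The only group size is in the sample-size text of the same section: "68 individuals in an independent cohort (34 LTB, 34 ATB) would provide a statistical power of 80" per cent, "to observe significant differences in top antibody features between tuberculosis infection and disease at an alpha level of 0.0005". The effect size behind it is a pilot finding in adults: "the partial correlation coefficient of 0.50 or higher was observed between diagnosis and antibody feature". No size is given for the healthy exposed children, the children with non-TB respiratory infection, or any age group.

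The Discussion states that "our data analysis is stratified across distinct age groups". The Data analysis section itself ties the four age groups to descriptive summaries of antibody concentrations.

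**The concern.** DeLong's method estimates the variance of the empirical AUC without a distributional model. The interval usually built from it is symmetric on the raw scale. As the AUC nears 1, its sampling distribution becomes skewed, and samples that overestimate the AUC also tend to give a small SE. The symmetric interval then sits too high: the lower limit is too close to the estimate, and the upper limit can pass 1. If the groups separate completely, the variance estimate is zero and the interval is [1, 1].

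This holds for a single feature named in advance, so it is separate from any optimism due to picking the best of many features. A reader judging whether a candidate assay is good enough looks at the lower limit, and that is the limit that errs.

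**Working it through.** **Inputs.** From the article: DeLong intervals; 34 versus 34; partial correlation r = 0.50; alpha 0.0005; 80% power; two covariates (age, gender). Assumed here: 95% confidence, two-sided alpha, normally distributed feature values in cases and controls.

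**The plan's own figure first.** Fisher's z for a partial correlation with k covariates:

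N = [(z(1 − α/2) + z(power)) / atanh(r)]² + 3 + k = [(3.481 + 0.842) / 0.5493]² + 3 + 2 = 61.9 + 5 = 66.9

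That is 67, or 68 in equal groups. The stated 68 reproduces (power at 68 is 0.810), and nothing below affects it.

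**AUC implied by the plan's effect size.** With equal groups, d = 2r/√(1 − r²) = 1/0.866 = 1.155. Under equal-variance normality, AUC = Φ(d/√2) = Φ(0.816) = 0.79.

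**Intervals compared.** Let A be the sample AUC from m cases and n controls, and S₁₀ and S₀₁ the sample variances of the case and control placement values.
- SE² = S₁₀/m + S₀₁/n
- Untransformed: A ± 1.96 SE
- Logit: ln[A/(1 − A)] ± 1.96 SE/[A(1 − A)], then back-transformed

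**Coverage at 34 versus 34** (20,000 replicates per cell, nominal 95%):

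| True AUC | Untransformed, equal SDs | Logit, equal SDs | Untransformed, case SD twice control SD | Logit, case SD twice control SD |
|---|---|---|---|---|
| 0.79 | 93.4% | 95.7% | 93.3% | 95.7% |
| 0.90 | 91.4% | 95.4% | 90.4% | 94.5% |
| 0.95 | 88.0% | 94.4% | 84.7% | 92.0% |

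Separate runs differed by at most about 0.6 points in the equal-SD columns.

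**Direction of the misses, untransformed, equal SDs.**
- AUC 0.79: lower limit above the truth in 5.7% of samples, in a run with 93.0% coverage. The other side is 100 − 93.0 − 5.7 = 1.3%.
- AUC 0.90: 8.1% against 0.5%.
- AUC 0.95: 11.5% against 0.3%. The nominal rate is 2.5% per side, so the lower limit errs 11.5/2.5 = 4.6 times too often.
- The upper limit exceeds 1 in 5% of samples at AUC 0.90 and 45% at 0.95.

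**One sample as illustration.** Take A = 0.95 and SE = 0.0265 (the median interval width of 0.104 in the unequal-SD runs at AUC 0.95, divided by 2 × 1.96). Untransformed: 0.95 ± 0.052 = 0.898 to 1.002. Logit: 2.944 ± 1.96 × 0.0265/(0.95 × 0.05) = 2.944 ± 1.093, which back-transforms to 0.864 to 0.983.

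**A larger control group.** With 34 cases and an assumed 100 controls, equal SDs, untransformed coverage is 92.0% at AUC 0.90 and 89.8% at 0.95, so extra controls alone do not remove the problem.

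**Age strata, conditional.** If AUCs were reported by age group, and if 34 split evenly over four groups (34/4 = 8.5), then 8 versus 9 gives untransformed coverage of 88.6%, 78.0% and 74.8% at AUC 0.79, 0.90 and 0.95. Intervals are [1, 1] in 1%, 9% and 25% of samples. The logit interval is undefined in those same samples, so the transform alone does not repair small strata.

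**The case against.** **The text does not say untransformed.** DeLong's contribution is a variance estimate, and the proposed fix keeps it. The scale could be set in a fuller plan. This stands as a limit on the finding. But the article does commit to a named method, and its unqualified name is ordinarily read as the raw-scale interval, so a sentence fixing the scale is worth having.

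**34 is not the size of every comparison.** It belongs to infection versus disease only. This stands: the sizes of the other comparisons are unknown, and 34 versus 100 is an assumption.

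**The high-AUC range may not be reached.** The one effect size given implies an AUC of 0.79, although the article says 0.50 or higher, and its Background and Discussion describe single antigens as having limited sensitivity. This stands, and it is the main reason the point is minor.

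**A reader might infer a target AUC of 0.96** by joining 98% specificity with 66% sensitivity. The article does not support this. These are two separate cut-off exercises within the strategies for combined interpretation, not a joint requirement on single features. The figure also depends on the equal-variance model. Suppose 65.4% of cases respond with a 5 SD shift and the rest look like controls. Sensitivity at 98% specificity is then about 66%, the AUC is 0.654 × 1.00 + 0.346 × 0.5 = 0.83, and untransformed coverage at 34 versus 34 is 93.0%.

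**A reader might also infer that the intervals fail in the age strata.** The article states neither an AUC by stratum nor a stratum size. The Discussion sentence on stratification is general and mentions no AUC.

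**AUC is not declared the main accuracy result.** This is correct: it stands beside Youden-based sensitivity and specificity, and no decision rule uses its interval.

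**Conclusion.** The concern holds as a minor point. If DeLong is applied in its usual raw-scale form at 34 versus 34, a nominal 95% interval covers about 93% at AUC 0.79, 91% at 0.90 and 88% at 0.95 under equal-variance normality (84.7% at 0.95 if the case SD is twice the control SD). The defect is better described as a lower limit that is too high than as an interval that is merely too narrow. It matters from about AUC 0.90 upwards and is small at the plan's own effect size.

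The conclusion rests on three assumptions: the untransformed reading, a 95% level, and the infection-versus-disease group size. The figures for age strata are a warning that depends on a reporting choice and group sizes the article does not state; they do not show that the plan fails there. DeLong's variance is not in dispute.

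**What to change.** State in the analysis plan that each AUC's 95% confidence interval uses DeLong's variance on the logit scale, back-transformed. Add that a score-type or exact-based interval is used when the sample AUC is 1, and for any AUC reported in a small age stratum (below about 15 in either group is a workable threshold).

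This takes about one sentence in the plan and one function in the code, with no effect on sample size or power. At 34 versus 34, coverage becomes about 95% under equal variances. It is not a complete cure: with the case SD twice the control SD, it is about 92% at AUC 0.95. The price is wider, asymmetric intervals for high AUCs, so the best features will look less certain than under the raw-scale form.
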